## **2. STUDY OBJECTIVES**

The primary objectives of this study are as follows:

- To determine the confirmed response rate of GSK1363089 treatment in subjects with gastric carcinoma or adenocarcinoma of the gastroesophageal junction or of the distal esophagus.
- To further evaluate the safety and tolerability of GSK1363089.

The secondary objectives of this study are as follows:

- To assess the disease stabilization rate, progression-free survival, duration of stable disease, and overall survival in subjects with gastric carcinoma or adenocarcinoma of the gastroesophageal junction or of the distal esophagus who are treated with GSK1363089.
- To characterize the PK and pharmacodynamic parameters of GSK1363089 in subjects with gastric carcinoma or adenocarcinoma of the gastroesophageal junction or of the distal esophagus.

Note: Each of the primary and secondary study objectives will be assessed for each dosing Cohort (1 – Intermittent 5 days on/9 days off dosing; 2 – daily dosing) separately and together.

The exploratory objectives of this study are as follows:

- To characterize the *c-MET* amplification status of patients in this study population and possible associations with response to GSK1363089 therapy. In addition, the mutational status as well as expression of *c-MET* and related genes and proteins (e.g., RON) and of relevant downstream targets may also be assessed.
- To evaluate the efficacy and safety profiles between two GSK1363089 dosing regimens - Intermittent 5 days on/9 days off and daily.
- To evaluate the effect of GSK1363089 treatment on potential pharmacodynamic markers of clinical activity in paired tumor biopsies (e.g. phospho-MET).

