### **3. STUDY DESIGN**

#### **3.1. Overview of Study Design**

This is a Phase 2, non-randomized, sequential-cohort, open-label, single-stage, safety and efficacy study, with an initial cohort of subjects enrolled onto the Intermittent 5&9 regimen, and then a 2nd cohort of subjects enrolled onto the daily regimen. Enrolment into Cohort 2 will not begin until enrolment into Cohort 1 has completed.

The estimated length of the study is 40 months for subject accrual and treatment. This study consists of a Pre-Treatment Period (screening and baseline evaluations), a Study Treatment Period, an optional Treatment Extension Period, and a Post-Treatment Period (including an end-of-treatment visit and an extended follow-up period). Throughout the study, AEs will be recorded as volunteered. Adverse events will be graded according to the NCI CTCAE v3.0. A copy of this grading scale will be provided to the study sites upon request, or it can be accessed at <http://ctep.cancer.gov/reporting/ctc.html>. All doses of GSK1363089 are to be administered on an empty stomach.

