#### **3.5. Requirement for Collection of Paired Tumor Biopsies**

Following the implementation of protocol Amendment 4.0, the collection of fresh, paired tumor biopsies will become a requirement rather than an option, to allow the assessment of the expression of pharmacodynamic markers of GSK1363089 activity, in particular relating to the c-MET pathway (e.g. total c-MET, phospho-MET and downstream markers).

After the first 6 subjects have been enrolled under Amendment 4.0 and have had paired tumor biopsies collected, enrolment will be put on temporary hold, while the safety and acceptability of collecting paired biopsies, plus the pharmacodynamic data, are reviewed

by GSK. If there are no safety concerns, and the pharmacodynamic objective with respect to c-MET has not been met, then subject enrolment will recommence and continue until the target number of subjects for Cohort 2 has been reached.

The safety and pharmacodynamic data for the paired tumor biopsies will continue to be reviewed on an ongoing basis. If a safety concern with obtaining the biopsies should ever arise and/or the pharmacodynamic objective with respect to c-MET has been met, then paired biopsies will no longer be required in this study. This will be communicated to the sites and IRBs by letter from GSK or its designee.

If any subject is not able to provide the second biopsy (i.e. at Day 5-8), then that subject will be allowed to continue on study and will be eligible for inclusion in the safety and efficacy assessments. However, if by so doing, this would prevent at least 12 subjects being enrolled who do provide paired biopsies, then an extra subject will be enrolled.

Instructions for the collection of paired tumor biopsies are provided in Section 5.9.2 and the Pharmacodynamic Laboratory Manual.

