#### **5.6.5. Ocular Assessments**

A complete eye examination by an ophthalmologist is required at baseline (up to 28 days before administration of study drug) and must be repeated every 6 months while on study drug and upon occurrence of new or worsening ocular symptoms (e.g. reduced visual acuity, new-onset night blindness) and discontinuation of study drug. Subjects currently on study must be re-consented and have a complete eye examination within 28 days after acceptance of protocol amendment 4.0. If study-drug discontinuation was not due to a new or worsening ocular event, the eye exam can occur up to and including the 30-day follow-up visit; and if the most recent exam was within 28 days a repeat exam will not be required. However, if the study-drug discontinuation was due to a new or worsening ocular event, the eye exam must be conducted as soon as possible (no later than 14 days from onset of the ocular event) and irrespective of whether the most recent exam was within 28 days.

All testing must be performed independently in each eye.

The following elements must be included in the ophthalmologic evaluation:

1. Best corrected visual acuity

2. Goldman visual field evaluation
3. Measurement of intraocular pressure
4. Slit lamp examination
5. Dilated fundoscopic examination including full field color retinal photographs

Light-dark adaptation testing, International Society for Clinical Electrophysiology of Vision (ISCEV) standard Electroretinography (ERG), and cancer-associated retinopathy antibody testing (e.g. Recombx™ CAR [Anti-Recoverin] Antibody Test, Athena Diagnostics, Inc.) must be performed in subjects who report poor vision in low illumination or have other symptoms suggestive of night blindness prior to initiation of therapy with GSK1363089. These tests can be conducted at any time up to 28 days prior to commencing study drug.

The presence of ocular symptoms or abnormalities on ophthalmologic evaluation at baseline does not preclude a subject from enrolling on the study. Such subjects may enroll on the trial if the treating physician, ophthalmologist and GSK study physician consider it safe to do so. However, it is recommended that counseling be provided to subjects with specific pre-existing ocular conditions before enrollment on the study. The following are suggested recommendations for such counseling:

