### **5.9.2. Fresh Frozen Tumor Tissue - Paired Tumor Biopsies**

The collection of paired tumor biopsies is required for all subjects who are enrolled in Cohort 2 after the implementation of Protocol Amendment 4.0. These samples will be used to study the effect of GSK1363089 on the expression of pharmacodynamic markers (e.g. total c-MET, phospho-MET and downstream markers).

Detailed instructions for sample preparation will be provided in the Pharmacodynamic Laboratory Manual and kits provided to the sites. The key points are summarized below:

- The baseline tumor biopsy should be collected as soon as possible prior to commencing study treatment, after all other inclusion and exclusion criteria are met, and at least 14 days after the completion of any prior anti-cancer therapy.
- The second tumor biopsy should be collected as close to Day 5 as possible, although it is acceptable to collect it up to Day 8 (Appendix B). It is important that the second tumor biopsy be obtained from the same organ as the pre-treatment biopsy, if at all possible.

Subjects should undergo core biopsies of either the primary gastroesophageal tumor or site of metastasis. The biopsies may be performed percutaneously under imaging guidance, or endoscopically, according to institutional practice. When endoscopic biopsies are performed we recommend at least 5-6 core biopsies with Jumbo forceps to ensure adequate yield of tissue. For the imaging-guided biopsies, 1-2 core biopsies will be performed with a 16-18-gauge needle. We recommend discussion of the feasibility of core biopsies with the radiologist/endoscopist performing the procedure to ensure that core biopsies can be indeed be performed.

Fine needle aspiration must not be used, as it would provide insufficient tumor tissue for studying the effect of GSK1363089 on the expression of pharmacodynamic markers.

All biopsies must be immediately embedded in OCT and snap frozen at -80 °C, in accordance with instructions in the Pharmacodynamic Laboratory Manual. It is highly recommended that a cytopathologist/pathologist be present during the tissue procurement procedures to ensure the presence of cancer cells in the specimen, immediately prior to snap freezing.

Note – these samples **must not** be used to provide paraffin-embedded tissue for determination of the subject's *c-MET*-amplification status. See instead Section 5.9.1.

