#### **8.1.4. Safety Analysis**

Safety endpoints include adverse events, laboratory data, and concomitant medications.

Adverse event verbatim terms recorded on the CRF will be mapped to preferred terms using the Medical Dictionary for Regulatory Activities (MedDRA).

A treatment emergent adverse event (TEAE) is defined as any adverse event with an onset date on or after date of first dose of study drug, or any ongoing event on date of first dose that worsens in severity after date of first dose. Only TEAE's with an onset date prior to date of last dose + 30 days will be tabulated in the summary tables.

TEAEs will be summarized for overall incidence, worst reported severity, and relationship to study treatment according to system organ class and preferred term.

Laboratory variables will be categorized according to the CTCAE v3.0 and will be summarized using mean change from baseline and shift in category from baseline.

All concomitant medications collected on the CRF's will be mapped to the WHO dictionary. Prior and concomitant medications will be summarized separately by ATC Level and Preferred Term.

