## APPENDIX H: SUMMARY OF CHANGES

The two major changes to this study associated with Amendment 4.0 are as follows:

1. Paired tumor biopsy samples, which were optional under Amendment 3.0, have been made mandatory for all newly-enrolled patients, and the timing window for collection of the second tumor biopsy sample has been changed to Day 5-8 from Day 8-15. This is described fully in Sections 3.5 and 5.9.2.
2. Following the observation of a potential ocular safety signal in the GSK1363089 clinical program, an ocular monitoring plan has been introduced in this amendment for ongoing and newly-enrolled subjects, including eye exams to be undertaken during screening and every 6 months while on study drug. Guidance on the interpretation of these assessments, plus possible extra eye exams, and potential changes to the dosing regimen, have also been provided. This is described in Sections 1.3.3.3.4 and 5.6.5.

In addition, a number of other changes have been made to the protocol as part of Amendment 4.0. The key changes are outlined and explained below, in the order in which they appear in the protocol:

3. Section 1.3.3.3.2 – two data errors have been corrected for the daily-dosing Phase I study (XL880-002); namely the number of subjects receiving 80 mg/day has been corrected from 3 to 9, and it has been noted that one of the 2 Grade 4 AEs (elevated GGT) was considered related to GSK1363089.
4. Section 2 – the objectives have been modified to match a change in the study endpoints and analysis plans described in Section 8.1 - two secondary efficacy endpoints have been removed (time to response and duration of response). In addition, the exploratory objectives have been modified to add the option to study the mutational status and expression of genes other than *c-MET* and to add the evaluation of the effect of GSK1363089 treatment on potential pharmacodynamic markers of clinical activity in paired tumor biopsies
5. Section 3.1 – the estimated time of study has been increased from 32 to 40 months, to allow for the slower recruitment rate associated with requiring paired tumor biopsies from all newly-enrolled subjects.
6. Section 3.1.1 – the requirement for archival tumor slides or tissue for FISH analysis of *c-MET* amplification status has been reinstated. In addition, a new requirement

for at least 4 subjects with *c-MET* amplification in Cohort 2, as defined by  $\geq 2$  copies of *c-MET* per copy of chromosome 7, has been introduced.

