7. Section 3.3.1 – the sample size requirements for *c-MET*-amplified subjects in each cohort are outlined, as well as 2 definitions of *c-MET* amplification.
8. A new section (3.5) has been introduced that describes the requirements for the collection of paired tumor biopsies, both at the subject level and the study level.
9. Section 4.2 (Inclusion Criteria) – two new criteria have been added (the requirement for archival [#3] and fresh [#4] tumor samples). In addition, 2 criteria have been modified:
  - #7 (renumbered as #9) - additional details have been added regarding minimum bilirubin levels for subjects with liver involvement (also in Section 5.6.1)
  - #12 (renumbered as #14) - for QTc intervals, the entry criterion is based on the average of 3 values if the first one is prolonged.
10. Section 4.4.4 – the guidance for the monitoring and treatment of hepatotoxicity has been updated to match language approved by GSK’s Global Safety Board.
11. The assessments and procedures for the pre-treatment, treatment and post-treatment periods (Sections 5.2-5.5) have been modified as follows - new ocular assessments have been added; the requirements for archival and fresh tumor samples have been updated; rules for conducting and interpreting ECHO or MUGA after ECG have been added; details of which radiologic tumor assessments to conduct have been added.
12. Section 5.6.2 and Appendix E – a definition of the urine protein creatinine (UPC) ratio has been added.
13. A new section (5.6.5) has been added, describing the ocular assessments required for ongoing and newly-enrolled subjects.
14. In Section 5.6.6, the instructions around the ECG assessments and when to do ECHO or MUGA have been clarified.
15. Section 5.7.1 has been renumbered as 5.8 and renamed as “Pharmacodynamic Assessments – Blood”. Additionally, samples are no longer required for assessment of circulating tumor and endothelial cells.
16. Section 5.7.2 (Potential Supplemental Pharmacodynamic Samples) has been deleted. The instructions for the collection of tumor biopsy samples is described in a new

Section (5.9.2).

17. The Tumor Assessment section has been renumbered as 5.9, and now includes all types of tumor assessment included in the protocol:
  - 5.9.1 – archival tumor tissue for FISH analysis to determine *c-MET*-amplification status.
  - 5.9.2 – fresh-frozen tumor tissue – paired tumor biopsies to study the effect of GSK1363089 on the expression of pharmacodynamic markers.

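### Eye examinations began with Amendment 4.0, so the planned ocular event rates, by cohort and pooled, mix examined with unexamined subjects

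*Combined protocol and SAP*

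**What the plan says.** Appendix H explains that, after a potential ocular signal in the drug's clinical programme, "an ocular monitoring plan has been introduced in this amendment for ongoing and newly-enrolled subjects". It also records that "A new section (5.6.5) has been added, describing the ocular assessments required for ongoing and newly-enrolled subjects". Scheduled eye exams are thus new in Amendment 4.0.

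Section 5.6.5 sets exams at baseline, every 6 months on drug, on new or worsening ocular symptoms, and at discontinuation. For subjects already enrolled it adds: "Subjects currently on study must be re-consented and have a complete eye examination within 28 days after acceptance of protocol amendment 4.0".

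On the order of enrolment, Section 3.1 says "Enrolment into Cohort 2 will not begin until enrolment into Cohort 1 has completed". Section 3.5, describing enrolment under Amendment 4.0 after a planned pause, says "subject enrolment will recommence and continue until the target number of subjects for Cohort 2 has been reached". Section 5.9.2 makes paired biopsies "required for all subjects who are enrolled in Cohort 2 after the implementation of Protocol Amendment 4.0".

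On analysis, Section 8.1.4 defines a TEAE as "any adverse event with an onset date on or after date of first dose of study drug", or an event ongoing at first dose that later worsens. Section 8.1.1 runs all safety analyses on the safety population, for each cohort and for both together. Section 2 makes safety and tolerability a primary objective, also by cohort and together, and lists as exploratory "To evaluate the efficacy and safety profiles between two GSK1363089 dosing regimens".

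**The concern.** An incidence table assumes that the event was looked for in a similar way in everyone in the denominator. Here the intensity of looking changed partway through the trial, and the change is tied to enrolment date and so, in part, to cohort. The safety analysis makes no allowance for it.

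Three readings are at stake. A pooled ocular rate divides by subjects who had no exam, so it understates what only an exam can reveal. A difference between regimens may reflect who was examined rather than which schedule was given. And where the first exam took place on drug, the TEAE definition asks for a comparison with a pre-dose state that no protocol exam recorded. The monitoring was added because of a possible ocular signal, so these are rates that readers will look for.

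**Working it through.** **Step 1: who was examined.** The plan states no ocular rate, so there is no figure to reproduce; the first step is to set the sections side by side. Exams start with Amendment 4.0 (Appendix H). Cohort 1 had finished enrolling before Cohort 2 opened (3.1), and enrolment under the amendment is into Cohort 2 (3.5, 5.9.2). This gives three groups:

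| Group | Pre-dose exam | Later exams |
|---|---|---|
| Off study before the amendment (Cohort 1 and any early Cohort 2) | none | none |
| Ongoing at the amendment (either cohort) | none | catch-up exam, then 6-monthly, symptom-triggered, discontinuation |
| Newly enrolled under the amendment (Cohort 2) | yes | 6-monthly, symptom-triggered, discontinuation |

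For the first group, ocular data rest on adverse events volunteered (3.1) or elicited by an open question (3.1.2). The Day 90 and 180 contacts (5.5.2) list no eye exam.

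**Step 2: classification.** A TEAE needs onset, or worsening of an ongoing event, after first dose. A symptom-free finding at a first on-drug exam has no earlier protocol exam to compare with, and no rule in 8.1.4 says how to class it. This needs no numerical assumption.

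**Step 3: size, by illustration.** Let *p* be the true ocular event rate, equal in both cohorts; *f* the share of a cohort examined; *s* the share of events reported without an exam. Assume that an exam finds every event. Then

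recorded rate = *p* × [*f* + (1 − *f*) × *s*].

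From the plan: 30 evaluable subjects per cohort (8.2), and at least 12 subjects sought with paired biopsies (3.5), used as a rough floor for new Cohort 2 enrolees. Assumed: *p* = 10%; *s* = 30%; examined share of Cohort 1, *f*₁, from 0 to 50%; examined share of Cohort 2, *f*₂, either 30/30 = 1 or 12/30 = 0.4 (the other 18 unexamined).

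- Cohort 1: *f*₁ = 0 gives 10% × 0.30 = 3.0%; *f*₁ = 0.2 gives 10% × (0.2 + 0.8 × 0.3) = 4.4%; *f*₁ = 0.5 gives 10% × (0.5 + 0.5 × 0.3) = 6.5%.
- Cohort 2: *f*₂ = 1 gives 10.0%; *f*₂ = 0.4 gives 10% × (0.4 + 0.6 × 0.3) = 5.8%.

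| Ratio, Cohort 2 to Cohort 1 (true ratio 1) | *f*₁ = 0 | *f*₁ = 0.2 | *f*₁ = 0.5 |
|---|---|---|---|
| *f*₂ = 1 | 3.3 | 2.3 | 1.5 |
| *f*₂ = 0.4 | 1.9 | 1.3 | 0.9 |

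At *f*₁ = 0 and *f*₂ = 1, varying *s* from 10% to 50% moves the ratio from 10 to 2. In the same corner with *s* = 30%, the chance of recording no ocular event among 30 subjects is 0.97³⁰ = 40% in Cohort 1 and 0.90³⁰ = 4% in Cohort 2.

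**Step 4: pooled rate of findings only an exam shows.** Here *s* = 0, so the pooled rate is *p* times the share examined. Over the same range that share runs from 12/60 = 20% to (15 + 30)/60 = 75%. The pooled rate is then 25% to 80% below the true rate.

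**The case against.** A reader might infer that Cohort 1 was hardly examined and that daily dosing will therefore look worse for the eye. The documents do not support this. The catch-up sentence covers every subject on study in either cohort, and the later exams then apply to them. The number of Cohort 1 subjects still on drug is not given. The November 2006 start, a reference accessed in April 2008 (so text at least 17 months later) and the median survival of under 10 months cited in Section 1.1 make a small number likely, but do not supply it. Section 5.9.2 also implies that some Cohort 2 subjects enrolled before the amendment, and they too lack a pre-dose exam. The divide is by amendment and exam status, and one cell of the table falls below 1.

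A reader might also infer that pre-existing lesions will be counted as treatment-emergent. That happens only if onset is dated to the exam, which the plan does not say, and eye-exam findings reach the TEAE tables only if recorded as adverse events. What stands is that such findings cannot be classed.

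Several points limit the importance. The regimen comparison is exploratory, non-randomized and across cohorts with different histology criteria. No between-cohort safety test is planned. With exams 6-monthly, many new subjects may have only baseline and discontinuation exams, and some late findings will fall outside the TEAE window of last dose plus 30 days. Section 8.1 leaves detail to a separate SAP. All of this lowers the stakes; none of it makes the denominators alike.

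**Conclusion.** The point holds as a question of ascertainment by enrolment date and exam status. No Cohort 1 subject has a protocol-required pre-dose eye exam; this is a firm inference from the order of enrolment, though no single sentence states it. Subjects off study before the amendment have no protocol eye exam at all.

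Analysed as written, the pooled rate of drug-emergent findings that only an exam shows is too low, the exploratory ocular contrast between cohorts is confounded, and findings at a first on-drug exam are unclassifiable. The distortion of the cohort ratio (0.9 to 3.3 at *s* = 30%) and the pooled shortfall (25% to 80%) are illustrations. They rest on assumed values of *p*, *s*, *f*₁ and *f*₂ and on perfect detection at exam; the documents give none of these.

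Restricting comparisons to symptom-reported events would not restore comparability. Amendment 4.0 also added re-consent for eye exams, counselling recommendations and contact with the study physician for ocular symptoms, and it lets ocular events that do not clearly meet the seriousness criteria be reported as serious (5.6.5). Reporting may have changed along with examination. This is a worthwhile, inexpensive improvement and does not touch the primary efficacy analysis.

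**What to change.** Leave the standard TEAE tables unchanged. Add to Section 8.1.4 and the SAP:

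1. An ocular summary by exam status: pre-dose exam plus at least one later exam; first exam on drug; never examined. Use the number examined as denominator for exam-detected findings. Give the count with only a pre-dose exam, so that the categories add up to the safety population; Section 5.6.5 waives the discontinuation exam in some subjects examined within the previous 28 days.
2. A separate row and listing for findings at a first on-drug exam, flagged as having no baseline exam. Do not remove them from the TEAE counts, since that could hide real drug-induced lesions.
3. A statement that between-cohort and pooled ocular rates, including those for symptom-reported events, are not to be read as comparable incidence.

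This needs no new visits and uses exams that the protocol already requires. The cost is one table, one listing and smaller denominators for exam-based rates. Exam-detected events must be identified by matching exam dates to adverse event records, because the protocol does not say that the case report form records how an event was found.
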